**Table 2 Tab2:** **Classification of morbidity in the present study**

Early morbidity	Late morbidity
0: No complications	1: Intestinal obstruction
1: Wound infection	2: Stenosis
2: Fluid collection or abscess	3: Chronic wound complications
3: Intra-abdominal bleeding	4: Others
4: Intraluminal bleeding	
5: Postoperative ileus	
6: Anastomosis stenosis	
7: Leakage	
8: Pancreatitis or fistula	
9: Pulmonary	
10: Urinary	
11: Renal	
12: Hepatic	
13: Cardiac	
14: Endocrine	
15: Others	

To evaluate overall survival as one of the oncologic outcomes and surgery-related mortality, all deaths of recruited patients during the RCT will be reported immediately, and the cause of death will be recorded.

For postoperative outcomes designated as secondary endpoints, the postoperative diet schedule, recovery of bowel movements, and pain scale will be investigated every morning before hospital discharge. Serum levels of whole blood leukocytes, hemoglobin, amylase, creatinine, and albumin are recorded as biochemical outcomes twice during recovery. Finally, the length of hospital stay and readmission will be evaluated.

To investigate the quality of life, the questionnaire suggested by the European Organization for Research and Treatment of Cancer (EORTC) will be used with web-based permission from EORTC. Patients are requested to complete the EROTC-QLQ 30 and STO 22 questionnaires perioperatively and at 4 weeks and 1 years postoperatively.

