### Study protocol

The Ajou ARO (Academic Research Organization) in Ajou University Hospital will manage this clinical trial. As soon as the participating surgeons obtain informed consent from the patients, researchers entered the patient information into an web-based electrical clinical report form (eCRF;http://clintrial.ajoumc.or.kr/klass02/). The beta version of eCRF system tested at each actual site before full implementation, to ensure data capture system and to reduce user error. The eCRF system is automatically given screening number according to the sequence in which the informed consent forms are received. And if patients meet the criteria for a randomization, then eCRF system assigned at each surgery group.. Finally, the system provides an allocation number with a pre-generated randomized code for those who are selected by inclusion and exclusion criteria. A randomized block design is applied for randomization with each investigator as the stratification factor (R 2.10.1). To maintain the properties of randomization, block size is not open to the investigators. The surgeons are immediately notified of the randomization results via e-mail. After notification, the surgeons let the patients know which type of operation they will undergo. Therefore, the surgeon and patient blinding is impossible owing to the nature of surgical RCT. However, the protocol recommends that ward staff members evaluating patient outcomes be blinded, if possible. If the surgeon does not perform the operation within 30 days after recruitment, the patients are excluded from the trial. These patients will need to be re-evaluated for re-recruitment into this RCT.

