### Outcome measurements

The primary endpoint of the KLASS-02 RCT is non-inferiority in the 3-year relapse-free survival rate after laparoscopic subtotal gastrectomy and extended lymphadenectomy for locally AGC compared with open conventional surgery. To measure this endpoint, the criteria for recurrence are suggested in detail. Recurrence can be detected on regular follow-up studies such as abdominopelvic CT in patients without specific symptoms through a formal radiology report. If the results of follow-up studies are suspicious, whole-body positron emission tomography-CT, magnetic resonance imaging of the liver, or laparoscopic exploration can be performed to confirm recurrence. Otherwise, patients can attend follow-ups at shorter intervals than the planned schedule. Patients with specific symptoms, such as abdominal mass, weight loss, or intestinal obstruction, which might coincide with recurrence, should be evaluated for recurrence immediately regardless of the follow-up schedule. Surgeon should report recurrence in enrolled patients by entering this information into the eCRF as soon as the recurrence is confirmed.

Secondary outcomes include postoperative morbidity and mortality, postoperative recovery, and quality of life. Complications are divided into early and late morbidities depending on time of occurrence. Early morbidity is defined as surgery-related complications occurring within 21 days postoperatively, and includes the events listed in Table 2. Complication severity is classified according to grading system suggested by Dindo D et al. [10]. Regarding postoperative morbidity, the operative time and blood loss volume are also recorded. In cases of conversion from laparoscopic to open surgery, the reason for conversion should be explained. The events related to late morbidity, which occur after the 28th postoperative day, are listed in Table 2.

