### Sample size calculation

The primary endpoint of this RCT is 3-year relapse-free survival of patients diagnosed with locally AGC. In an RCT conducted by Sakuramoto et al. [9], the 3-year relapse-free survival of gastric cancer patients who received TS-1 adjuvant chemotherapy and were diagnosed with stage II or III cancer on pathology from curative gastrectomy with D2 lymph node resection was 72% (hazard rate = 0.11). Therefore, the hazard rate of patients who underwent open conventional surgery in the control condition was 0.11 in the 3 year. In addition, the margin of non-inferiority assumed a hazard ratio (HR; hazard rate of group A/hazard rate of group B) of 1.43 according to the study design in the Sakuramoto et al., in which the HR of the surgery-only group was compared with that of the adjuvant group. The null hypothesis was assigned as HR ≥ HR_0_, and the alternative hypothesis as HR < HR_0_. Type I error was set at 0.25 (one-sided) with 90% power, and the sample size was calculated using the log-rank test for non-inferiority (PASS 12. NCSS, LLC. Kaysville, Utah, USA. www.ncss.com.).

As a result, a total of 1,050 patients (525 patients per group) with 330 target event as recurrence are required when we consider a 10% dropout rate.

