### Patient groups for statistical analysis

The efficacy for the primary and secondary outcomes will be evaluated in different groups of patients according to the surgical results. Except for the patients who are not undergoing surgery or have unresectable tumors, all patients will be included in the intention-to-treat (IIT) group. The postoperative recovery, morbidity and mortality, quality of life, and overall survival will be evaluated for the patients in IIT group. The 3-year relapse-free survival will be analyzed for patients in the full analysis set (FAS) group. ITT group patients who cannot undergo curative resection and have synchronous tumors or distant metastases un-defined at the screening step, will be additionally excluded from the FAS group. If patients did not comply with protocol because of various reasons like as conversion of surgical type, total resection and follow up loss, then they will be excluded from the per-protocol (PP) group. When the difference between the FAS and PP groups exceeds 10% of the total recruitment number, statistical analysis with the PP group patients will be performed. This RCT is schematically described in Figure 1. For safety analysis, patients in FAS group are examined with their actual treated surgery.

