**Figure 1 Fig1:**
[figure not shown]
Overview of the Korean Laparoscopic Surgical Society (KLASS)-02 randomized controlled trial (RCT) design. RFS; relapse free survival, FU; follow up, PP; per protocol.

For analysis of relapse-free or overall survival, Kaplan-Meier curve analysis with log-rank tests will be used. To investigate the different proportions of patients with morbidity, mortality, or other categorical data between 2 groups, chi-square or Fisher’s extract tests will be applied. Continuous variables such as length of hospital will be evaluated using student t- or Mann–Whitney U tests. The level of significance will be set at 5%.

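### The only test stated for continuous outcomes makes no use of the first quality-of-life questionnaire, whose timing does not guarantee a baseline: a small, precision-only point on a secondary outcome

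*Protocol article*

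**What the plan says.** Quality of life is a secondary outcome. The Outcome measurements section states: "Secondary outcomes include postoperative morbidity and mortality, postoperative recovery, and quality of life". The same section, after Table 2, gives the schedule: "Patients are requested to complete the EROTC-QLQ 30 and STO 22 questionnaires perioperatively and at 4 weeks and 1 years postoperatively".

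The analysis set is given under Patient groups for statistical analysis: "The postoperative recovery, morbidity and mortality, quality of life, and overall survival will be evaluated for the patients in IIT group". At the end of that section, after Figure 1, comes the only sentence on testing continuous data: "Continuous variables such as length of hospital will be evaluated using student t- or Mann–Whitney U tests". The significance level is 5%, with sidedness not stated. No covariate, change score or repeated-measures model is named.

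The Study protocol section sets the order of events. Consent is followed by randomisation, stratified by investigator, and the surgeon is notified at once by e-mail. Then: "After notification, the surgeons let the patients know which type of operation they will undergo". The operation must follow within 30 days of recruitment.

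**The concern.** There are two linked issues.

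**Method.** Student t and Mann–Whitney tests compare two groups on one variable. Applied to a follow-up score, they ignore what the same patient reported on the first form. Scores on one instrument from one person are usually correlated over time, and adjusting for the first score then gives a tighter estimate from forms that are collected anyway.

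**Timing.** Adjustment is sound only if the first score cannot have been affected by treatment. *Perioperatively* can mean before or after the operation. A form completed after surgery may already carry part of the treatment effect, and adjusting for it could remove some of the difference being estimated. A form completed before surgery but after the patient has learned the allocation is answered by an unblinded patient. The Discussion accepts that lack of blinding invites subjective measurement and relies on objective endpoints as the safeguard. Self-reported quality of life does not have that protection.

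At stake are the width of the confidence intervals for the quality-of-life comparisons and whether the first form can be used as a baseline at all. An analysis plan written later can choose the model, but it cannot change when a form was completed.

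**Working it through.** The article gives no effect size, standard deviation, correlation or power for quality of life, so there is no quality-of-life figure to reproduce. The check asks what adjustment would be worth at the stated trial size.

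**Inputs**
- Patients per group: 525 (Sample size calculation).
- With 10% loss: 525 × 0.90 = 472.5, taken as 472. The 10% is the article's dropout rate for the sample size. Applying it to questionnaires is an assumption.
- Test level: 5%, taken as two-sided.
- Correlation r between the first and the follow-up score: **not in the documents**; 0.2 to 0.7 assumed.

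**Unadjusted test.** In SD units, the difference detectable with 80% power is (1.960 + 0.842) × √(2/n).
- n = 525: 2.802 × √(2/525) = 0.173 SD.
- n = 472: 2.802 × √(2/472) = 0.182 SD.

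**ANCOVA.** The variance of the treatment difference is multiplied by 1 − r², so the standard error is multiplied by √(1 − r²). The equivalent unadjusted sample is n/(1 − r²).

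**Change score.** A t-test on change from the first score would also fit the article's sentence. Its variance factor, with equal SDs at both times, is 2(1 − r).

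Results for 525 per group. Power is for the difference at which the unadjusted test has 80%.

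| r | 1 − r² | SE reduction | ANCOVA power | Detectable at 80%, ANCOVA (SD) | Equivalent n per group | Change-score factor | Change-score power |
|---|---|---|---|---|---|---|---|
| 0.2 | 0.96 | 2.0% | 81.6% | 0.169 | 547 | 1.6 | 60.1% |
| 0.3 | 0.91 | 4.6% | 83.6% | 0.165 | 577 | 1.4 | 65.8% |
| 0.4 | 0.84 | 8.3% | 86.4% | 0.158 | 625 | 1.2 | 72.5% |
| 0.5 | 0.75 | 13.4% | 89.9% | 0.150 | 700 | 1.0 | 80.0% |
| 0.6 | 0.64 | 20.0% | 93.8% | 0.138 | 820 | 0.8 | 87.9% |
| 0.7 | 0.51 | 28.6% | 97.5% | 0.123 | 1,029 | 0.6 | 95.1% |

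Worked line, r = 0.5: 1 − 0.25 = 0.75; √0.75 = 0.866, so the SE falls by 13.4%; 525/0.75 = 700.

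With 472 per group, the detectable difference under ANCOVA runs from 0.179 SD (r = 0.2) to 0.130 SD (r = 0.7).

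ANCOVA is more precise than the follow-up comparison and the change-score test at every r shown. The change-score test is worse than ignoring the first form when r is below 0.5. The figures are for the t-test; the Mann–Whitney loss was not calculated.

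**Timing.** The protocol section fixes the order consent, randomisation, disclosure to the patient, then surgery within 30 days of recruitment. The quality-of-life schedule fixes only the word *perioperatively*. No sentence places the first form before disclosure, or before the incision. A form completed at any of these stages would comply.

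**The case against.** The best case against is that the article never says quality of life will be compared without a baseline. The sentence on continuous variables is generic. Its one example, length of stay, has no baseline, and it neither names quality of life nor rules out adjustment. A condensed article commonly leaves the model for a secondary patient-reported outcome to the full protocol or analysis plan, and neither is shown. This stands, and it is why the point is conditional on the stated test being the one applied. The sentence is nevertheless the only stated rule that could cover these scores, so proposing a better method than the stated one is fair.

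The schedule also sets *perioperatively* against two postoperative times, so a preoperative form is a natural reading. That is plausible, but it is not stated, and it does not settle whether the form precedes disclosure.

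It can further be said that the two halves pull apart: if the first form is not a clean baseline, there is no precision to recover. That is correct. The gain in the table is available only for forms completed before surgery, so the timing instruction has to come first.

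A reader might infer more than this: that the plan discards baseline data, that the unadjusted comparison is biased, or that a hoped-for quality-of-life benefit is put at risk. The documents support none of these. The first is an inference from the generic sentence. The second is wrong, because a randomised comparison without covariates is valid and its error rate already allows for chance imbalance. On the third, the Discussion expects improved postoperative recovery and does not name quality of life as an expected benefit.

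**Conclusion.** The point holds as a minor efficiency and timing matter on a secondary outcome. If the stated t- or Mann–Whitney test is used for the EORTC scores, it forgoes a standard-error reduction of about 2% at r = 0.2 to 29% at r = 0.7. This range rests on an assumed correlation and on a first form completed before surgery. At the low end the gain is negligible, and 525 per group already detects 0.173 SD at 80% power without adjustment. The primary endpoint, its type I error and the sample size are unaffected.

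The timing half needs no assumed figure: the wording as published does not secure a baseline, and this cannot be repaired once forms are in.

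**What to change.** 1. **Timing.** State that the first EORTC questionnaire is completed before surgery and before the patient is told the allocation.
2. **Model.** State that the 4-week and 1-year scores are analysed by ANCOVA, or by a repeated-measures model, with the first score and the stratification factor (investigator) as covariates. Report the adjusted difference with its 95% CI.
3. **Late forms.** State that a form completed after surgery is not used as a covariate. For forms already collected, compare the completion date with the dates of allocation and surgery where these are recorded.

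The cost is a few sentences in the analysis text and one instruction to sites; no new visits, questionnaires or patients are needed. If the full protocol or analysis plan already says this, confirming it is enough.

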### Sample size calculation

The primary endpoint of this RCT is 3-year relapse-free survival of patients diagnosed with locally AGC. In an RCT conducted by Sakuramoto et al. [9], the 3-year relapse-free survival of gastric cancer patients who received TS-1 adjuvant chemotherapy and were diagnosed with stage II or III cancer on pathology from curative gastrectomy with D2 lymph node resection was 72% (hazard rate = 0.11). Therefore, the hazard rate of patients who underwent open conventional surgery in the control condition was 0.11 in the 3 year. In addition, the margin of non-inferiority assumed a hazard ratio (HR; hazard rate of group A/hazard rate of group B) of 1.43 according to the study design in the Sakuramoto et al., in which the HR of the surgery-only group was compared with that of the adjuvant group. The null hypothesis was assigned as HR ≥ HR_0_, and the alternative hypothesis as HR < HR_0_. Type I error was set at 0.25 (one-sided) with 90% power, and the sample size was calculated using the log-rank test for non-inferiority (PASS 12. NCSS, LLC. Kaysville, Utah, USA. www.ncss.com.).

As a result, a total of 1,050 patients (525 patients per group) with 330 target event as recurrence are required when we consider a 10% dropout rate.

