### Safety assessment for early morbidity

When the safety analysis group reaches 484 patients, analysis will be performed to evaluate the safety of laparoscopic subtotal gastrectomy with D2 lymphadenectomy. Considering the reports of Sano et al. [11] and Deguili et al. [12], the complication rate of standard gastrectomy with D2 lymph node dissection was estimated at 20.9% and the margin of non-inferiority for the complication rate was assumed to be 12%. With a type I error of 0.025 (one-sided) and 90% power, 242 patients in each safety analysis group are required. When a total of 484 patients are enrolled in the safety analysis groups, the steering committee will decide whether this trial would be continued according to the results of this safety analysis.

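### The primary non-inferiority test is given a one-sided type I error of 0.25, which the plan's own 330 events contradict; they correspond to 0.025

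*Protocol article*

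**What the plan says.** The Sample size calculation section of the protocol article defines the primary test. It sets the margin, "the margin of non-inferiority assumed a hazard ratio (HR; hazard rate of group A/hazard rate of group B) of 1.43", and the hypotheses, "The null hypothesis was assigned as HR ≥ HR_0_, and the alternative hypothesis as HR < HR_0". The error rates follow: "Type I error was set at 0.25 (one-sided) with 90% power". The method is named: "the sample size was calculated using the log-rank test for non-inferiority". The section then gives the result: "a total of 1,050 patients (525 patients per group) with 330 target event as recurrence are required when we consider a 10% dropout rate".

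Two other places bear on the level:

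- Safety assessment for early morbidity, the plan's other non-inferiority comparison: "With a type I error of 0.025 (one-sided) and 90% power, 242 patients in each safety analysis group are required".
- The last sentence of the statistical methods, after Figure 1: "The level of significance will be set at 5" per cent. It gives no sides and follows a list of log-rank, chi-square, Fisher, t and Mann-Whitney tests.

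The Interim analysis section uses 0.001, but for a look at half the events aimed at showing inferiority. It says nothing about the final level. Nowhere does the article restate, justify or correct 0.25.

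**The concern.** In a non-inferiority trial the one-sided type I error is the chance of declaring the new procedure acceptable when its true effect lies exactly at the margin. A value of 0.25 is ten times the level that the same article uses for its safety comparison, and no reason is given for the difference. It also looks far too lenient to need 330 events at a margin of 1.43.

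What is at stake is the threshold for the trial's main claim. A reader who takes the article as the public record of that threshold finds 0.25 for the primary test and, later, a 5% level without sides. Neither, as printed, clearly states the level at which the trial was sized.

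**Working it through.** **Inputs.** From the Sample size calculation section: margin hazard ratio 1.43, power 90%, 525 patients per group (1:1), 330 target events, 10% dropout, control hazard 0.11 per year (check: −ln(0.72)/3 = 0.1095). Assumed, because the article does not state it: true hazard ratio 1 under the alternative. Also assumed: group A is the laparoscopic arm, the only reading under which the stated hypotheses test its non-inferiority.

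**Step 1: events required.** The Schoenfeld formula with equal allocation is

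D = 4 (z_α + z_0.90)² / (ln 1.43)², with z_0.90 = 1.2816 and (ln 1.43)² = 0.3577² = 0.1279.

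- α = 0.025: 4 × (1.9600 + 1.2816)² / 0.1279 = 328.5
- α = 0.05: 4 × (1.6449 + 1.2816)² / 0.1279 = 267.8
- α = 0.25: 4 × (0.6745 + 1.2816)² / 0.1279 = 119.6

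The Freedman version, D = (z_α + z_0.90)² × (2.43/0.43)², is a cross-check. Rounded up:

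| One-sided α | Schoenfeld | Freedman | Power at 330 events (Schoenfeld) |
|---|---|---|---|
| 0.025 | 329 | 336 | 90.1% |
| 0.05 | 268 | 274 | 94.6% |
| 0.125 (0.25 halved) | 185 | 189 | 98.2% |
| 0.25 (as printed) | 120 | 123 | 99.5% |

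Only 0.025 reproduces the plan's 330 events and its 90% power together.

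**Step 2: the level implied by 330 events.** Solving for α at 90% power:

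- Schoenfeld: 1 − Φ(√(330/4) × ln 1.43 − 1.2816) = 0.0246
- Freedman: 1 − Φ(√330 × 0.43/2.43 − 1.2816) = 0.0266

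**Step 3: patients.** The article states no accrual or follow-up period for the calculation, so several were tried: accrual from 0 to 5 years with 3 years of further follow-up, and 3 years with 2. The control hazard was 0.11 and the total was divided by 0.90 for dropout.

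- α = 0.25: 299 to 487 patients, never near 1,050.
- α = 0.025: 818 to 1,329. With 2 years of accrual and 3 of follow-up it is 1,031 (Schoenfeld) or 1,053 (Freedman).
- α = 0.05: 667 to 1,084.

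The patient number therefore rules out 0.25 under every pattern tried. It does not separate 0.025 from 0.05; the event count does that.

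**Step 4: the companion calculation.** For the safety comparison, with complication rate 20.9% and margin 12 percentage points at 0.025 one-sided:

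(1.9600 + 1.2816)² × 2 × 0.209 × 0.791 / 0.12² = 241.3, that is 242 per group, exactly as stated.

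At 0.25 the same calculation gives 88.

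**Step 5: what each level would accept.** With 330 events the standard error of the log hazard ratio is about 2/√330 = 0.1101. Non-inferiority is declared when the observed hazard ratio is below exp(ln 1.43 − z_α × 0.1101):

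- α = 0.025: 1.152
- α = 0.05: 1.193
- α = 0.25: 1.328

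**The case against.** The strongest reply is that this is a misprint and not a design flaw. The article's own numbers show that the trial was sized at 0.025, and the safety section prints 0.025 in a parallel sentence. The 25% false-claim rate only restates what an α of 0.25 means; nothing beyond that one figure suggests the trial would be run that way. This stands as a description of how the error arose, and the sample size needs no change. It does not remove the error: the wrong figure is the level of the primary test, and readers should not have to work it out backwards.

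Second, the 5% level need not conflict with anything. It closes a list of ordinary comparisons where 5% is usually two-sided, and two-sided 5% is the same threshold as one-sided 0.025. This is largely right. What remains is that the sides are not stated and the sentence is not linked to the primary test. Only if 5% were applied one-sided would the error rate be twice the 0.025 that 330 events support at 90% power.

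Third, the match with 0.025 depends on a true hazard ratio of 1. Using D = 4 (z_α + z_0.90)² / (ln(1.43/HR))², 330 events at 90% power would also follow from α = 0.25 with a true hazard ratio of about 1.15, or α = 0.05 with about 1.04. That is correct arithmetic, but the article mentions no expected disadvantage for laparoscopy, and equality is the conventional assumption.

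Fourth, a confidence-interval rule is a detail that a condensed article may leave to the full protocol or analysis plan. Its absence is indeed no fault. It is offered below only as an equivalent statement that makes a repeat of the slip less likely.

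**Conclusion.** The concern holds: the type I error for the primary test is wrong as written. Assuming a true hazard ratio of 1, the printed 0.25 needs about 120 events and would give 99.5% power at 330, whereas 0.025 one-sided gives 328.5 events and 90.1% power. The figure is almost certainly a slip for 0.025.

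The consequence is conditional on the text being followed as printed. In that case the limit on the observed hazard ratio would move from about 1.15 to about 1.33, and the chance of a false non-inferiority claim at a true hazard ratio of 1.43 would be 25% instead of 2.5%. Margin, power, events and patient number are consistent with one another once the level is read as 0.025. The correction is a must because the figure fixes the primary decision rule.

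**What to change.** 1. In Sample size calculation, replace 0.25 with 0.025 (one-sided).
2. Add one sentence in the same place: non-inferiority is declared if the upper limit of the two-sided 95% confidence interval for the relapse-free survival hazard ratio, laparoscopic over open, is below 1.43. This is the same rule as the one-sided 0.025 test and also settles the direction of the ratio.
3. In the closing sentence of the statistical methods, state that the 5% level is two-sided and that it covers the superiority-type comparisons, not the primary non-inferiority test.

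The cost is one figure and a sentence or two of text. The 330 events and 1,050 patients stay as they are. If an analysis plan exists, its stated level should be checked against the corrected figure.

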#### Inclusion criteria

Patients aged >20 and <80 yearsPatients with an Eastern Cooperative Oncology Group (ECOG) performance status of 0 or 1Patients with American Society of Anesthesiology score of class I to IIIPatients diagnosed with gastric adenocarcinoma that is possible to be curatively resected by subtotal gastrectomyPatients with primary gastric carcinoma that has invaded into the muscle propria, not into an adjacent organ (cT2 to cT4a) in preoperative studiesPatients with no lymph node metastasis or limited perigastric lymph node metastasis (including lymph nodes around the left gastric artery) in preoperative studiesPatients who agree to participate in the clinical study through informed consent.

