#### Postoperative care

The ward staff will evaluate the patients every morning and afternoon for the presence of any issues affecting the patients’ recovery. The degree of pain, diet schedule, and gas out were daily recorded until discharged, and laboratory findings are recorded on the first and fifth postoperative day. After surgery, the surgeon can progress the diet schedule from sips of water to a soft diet according to the patient’s condition. If the patients are in good condition 2 or 3 days after starting a soft diet and do not have complaints regarding their status, they can be discharged from the hospital.

After fully recovering from surgery, patients diagnosed with Stage II (except T1) or Stage III cancer in the final pathology report will be recommended for adjuvant chemotherapy based on 5-fluorouracil administration. Adjuvant chemotherapy will be started from 4–6 weeks postoperatively, if the patients’ general condition is suitable for chemotherapy.

After curative resection, all patients will be regularly evaluated for disease recurrence postoperatively every 3 or 6 months over a 3-year period. Abdominopelvic computed tomography (CT), serum tumor markers (CEA and CA19-9), and other parameters can be included in studies for regular follow-up.

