### Interim analysis

When the number of target event as recurrent cases reaches half the expected number of the calculated sample size, we will perform an interim analysis to identify if clear evidence exists that laparoscopic surgery is inferior to open surgery, and should not be used. The interim analysis will be conducted by the Haybittle-Peto interim monitoring boundary method, with type I error set at 0.001 according to the previous report of Freidin et al. [13].

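### With the stated 3 years of recurrence surveillance, 1,050 patients give about 266 to 295 events and 83 to 87% power, not the planned 330 events and 90%

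*Protocol article*

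**What the plan says.** The article's section on sample size calculation takes its control rate from an adjuvant chemotherapy trial in patients who "were diagnosed with stage II or III cancer on pathology from curative gastrectomy with D2 lymph node resection was 72" per cent, with a hazard rate of 0.11. It states that "the margin of non-inferiority assumed a hazard ratio (HR; hazard rate of group A/hazard rate of group B) of 1.43" and that "Type I error was set at 0.25 (one-sided) with 90% power". The result is "a total of 1,050 patients (525 patients per group) with 330 target event as recurrence are required when we consider a 10% dropout rate".

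The postoperative care section gives the only follow-up length in the article: after curative resection "all patients will be regularly evaluated for disease recurrence postoperatively every 3 or 6 months over a 3-year period". The primary endpoint, under outcome measurements, is 3-year relapse-free survival (RFS).

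Entry is by clinical stage. The inclusion criteria ask for a tumour that "has invaded into the muscle propria, not into an adjacent organ (cT2 to cT4a"), and node-negative patients are eligible. Adjuvant chemotherapy is recommended only for certain stage II and for stage III patients on final pathology, so the plan foresees other pathological stages.

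The interim analysis is triggered "When the number of target event as recurrent cases reaches half the expected number of the calculated sample size".

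**The concern.** The event target, the number of patients and the follow-up length have to agree, because two of them determine the third at a given hazard. Here the hazard and the 3-year surveillance imply clearly fewer events than 330.

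The stake is the stated power. In a non-inferiority trial, lost power means a greater chance of an inconclusive result when the two operations are in truth equivalent. The interim look is affected too. Half of 330 is 165 events, which would be 165/266 = 62% of the events expected at 3 years, not half.

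Two related points bear on the same count. The control rate belongs to a population selected by pathological stage, and the events to be counted are described as recurrences although the endpoint is RFS.

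**Working it through.** **Inputs from the article.** Control hazard 0.11 per year (check: −ln 0.72 / 3 = 0.1095); margin HR 1.43; power 90%; 1:1 allocation; N = 1,050; dropout 10%, leaving 945; surveillance 3 years per patient.

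**Assumptions.** True HR = 1; exponential event times; one-sided alpha 0.025.

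**1. The plan's 330 events.** Schoenfeld: d = 4(z_α + z_β)² / (ln 1.43)².
- Alpha 0.025: 4(1.960 + 1.282)² / 0.3577² = 329, which matches 330.
- Alpha 0.25 as printed: 4(0.674 + 1.282)² / 0.3577² = 120, which does not match.

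So 0.025 was evidently used, and it is used below. Power with d events is Φ(ln 1.43 × √d / 2 − 1.96). At d = 330 this is 90.1%.

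**2. Events in 3 years per patient.** Event probability = 1 − exp(−0.11 × 3) = 0.281. For dropout spread over time, the dropout hazard is −ln 0.9 / 3 = 0.0351, and the probability of an observed event is 0.11/0.1451 × (1 − exp(−0.1451 × 3)) = 0.2675.

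| Dropout | Events | Power |
|---|---|---|
| 10%, all early | 945 × 0.281 = 266 | 83% |
| 10%, spread over 3 years | 1,050 × 0.2675 = 281 | 85% |
| None | 1,050 × 0.281 = 295 | 87% |

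**3. What 330 events would need.**
- Time per patient from 945: −ln(1 − 330/945) / 0.11 = 3.9 years. From 1,050: −ln(1 − 330/1,050) / 0.11 = 3.4 years.
- Patients at a fixed 3 years: 330 / 0.281 = 1,174, and 1,174 / 0.9 = about 1,305.

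**4. A schedule that does fit.** With uniform accrual over A years and follow-up to a common date F years after accrual ends, the event probability is 1 − [exp(−0.11F) − exp(−0.11(A + F))] / (0.11A). For A = 2 and F = 3 it is 0.355. That gives 945 × 0.355 = 335 events and a required N of 329 / 0.355 / 0.9 = about 1,031, within 2% of 1,050. The accrual time is an assumption. A = 4 with F = 2 also fits (about 331 events). In either case early patients are followed for RFS beyond 3 years.

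**5. Stage mix, illustration only.** Let a share s have pathological stage I with 3-year RFS r, and the rest 72%. Events = 945 × [s(1 − r) + (1 − s) × 0.28].
- s = 10%, r = 90%: 248 events, power 80%.
- s = 40%, r = 95%: 178 events, power 66%.

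Neither s nor r is in the article. The calculation shows the direction and how sensitive the count is.

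**The case against.** The strongest reply is that the design is event-based. The article says 330 events are required, and it triggers the interim by event count. The postoperative care section sets a surveillance schedule. It does not say that patients are censored at 3 years or when the analysis takes place. An accrual time of about 2 years with a common closing date reproduces both 1,050 and 330, and an article may leave accrual and cut-off to the full protocol. If the analysis waits for 330 events, power is 90%, and a low event rate delays the result without lowering power.

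Much of this stands. A reader might infer that 330 events can never be reached, or that power is simply 83%. The article supports neither: both need every patient to be censored at 3 years, and 83% also needs all dropouts to contribute no events. Expected counts would also be higher if laparoscopy were worse: at HR 1.43 throughout, the three-year probabilities of 0.281 and 0.376 average 0.329, giving 311 events from 945 patients or 345 from 1,050.

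What does not stand is that accrual time settles the matter. A longer accrual adds events only if early patients remain under recurrence surveillance after their third postoperative year. The article counts the 3 years from surgery and names no later date. Waiting likewise helps only if surveillance goes on.

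On the event wording, a reader might infer that operative deaths would be left out of the primary comparison. That goes too far. The analysis is named as one of relapse-free survival, and all deaths and their causes are recorded. Only the descriptions of the target and of the interim trigger are limited to recurrence.

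**Conclusion.** The point holds conditionally. Followed as written, with 3 years of recurrence surveillance per patient, the plan yields about 266 to 295 events and 83 to 87% power, short of its own 330 and 90% under every dropout assumption tried. This rests on hazard 0.11, equal arms and one-sided alpha 0.025. The 330 is itself correct for 90% power, and 1,050 patients can supply it if RFS follow-up of early enrollees continues past 3 years.

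The use of a stage II/III control rate for a clinically staged population makes fewer events likely, but the article gives no basis for a size. The recurrence-only wording of the target and the interim trigger does not match an RFS endpoint and needs correcting.

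**What to change.** Choose one of two routes and state it.

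1. Keep 3-year follow-up and restate the design: about 266 to 295 expected events and 83 to 87% power. Add a sensitivity range for a higher control RFS. For example, at an assumed 80%, 945 × 0.20 = 189 events, and power is Φ(0.3577 × √189 / 2 − 1.96) = 69%.
2. Keep 330 events and 90% power: tie the final analysis to the 330th event or to a common closing date, state the accrual period, and say that RFS follow-up of all patients continues to that date.

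Under either route, define the counted event as recurrence or death from any cause, and use it both for the target and for the half-way interim trigger. Confirm that the one-sided type I error is 0.025.

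The cost is a less favourable power figure under the first route, or some follow-up beyond 3 years for early enrollees under the second. Neither needs extra patients.
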